## Results

This protocol was originally designed in August 2021. Alpha and beta testing on Evolution Health’s staging environment began in October 2021. The protocol was revised in October 2021, and the experiment was pushed live in November 2021. We exceeded the sample size requirements in each arm and concluded data collection in May 2022.

## Discussion

### Hypotheses

We hypothesize that members will engage with the prompts and nudges. We also hypothesize that the secondary results will generate insights on the types of prompts and nudges that are the most likely to result in engagement among members. This finding may be important, as dose-response relationships have been observed in digital health interventions [8,51].

### Practical Implications

If we learn that the prompts are used by members, the arm 2 or arm 3 home page will become the default user home page for all new and existing members.

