**Results:**

The experiment was designed in August 2021 and was launched in November 2021. Initially, we will measure engagement with the tips and the to-do checklist by calculating the frequency of use by age and gender. If members do engage, we will then, according to age and gender, examine whether nudges and prompts result in higher course completion rates and whether specific types of prompts and nudges are more popular than others.

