### Objective

The main objective of our 3-arm randomized controlled trial is to test whether registered members in two well-established, self-guided digital health courses for anxiety and depression will engage with four different types of nudges and prompts, and whether engaging with nudges and prompts increases engagement within the courses.

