### Intervention Groups

Members allocated to the first arm will be presented with a member home page that contains no behavioral prompts. Figure 3 is a screenshot of an arm 1 homepage for a member who chooses to engage with the depression course.

Members allocated to the second arm will be presented with a member page that contains a *Tip-of-the-Day* section containing directive content. The randomization strategy for the 35 directive tips is randomization without replacement. Figure 4 is a screenshot of an arm 2 homepage for a member who chooses to engage with the depression course.

Members allocated to the third arm will be presented with two sections that contain interactive prompts. The first is a *Tip-of-the-Day* section containing social proof and present bias content. At each log in, members will see a new tip. The randomization strategy for the tips is randomization without replacement. There are 15 social proof tips and 15 present bias tips.

In addition to the tips of the day, the third arm will also feature a to-do checklist that lists interactive course components. When a member clicks on an interactive component, they will be brought to the exercise. When they complete the exercise, the item is marked as complete with a check mark. Figure 5 is a screenshot of an arm 3 homepage for a member who chooses to engage with the depression course.

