### Primary Outcome: Engagement With Tips and To-do Items

We will first measure engagement with the tips and to-do items in arms 2 and 3. We will compare the frequency of engagement with each nudge and behavioral prompt by age and gender. A member’s engagement with tips will be measured as the proportion of tips that were clicked. Specifically, it will be a value between 0 and 1, calculated as the number of tips that a member clicked divided by the number of tips that were presented to the member. Engagement with to-do items will be measured as the number of to-do items that a member clicked, and course component completion rates will be measured as the number of course components that a member completed. All comparisons between arms 2 and 3 will be conducted by using an independent sample 1-tailed *t* test; a conventional α level (.05) for statistical significance will be used.

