### Secondary Outcomes: Completion of Course Components

A secondary outcome of this experiment is to test whether the presentation of tips and to-do items increases the overall completion of course content. We will achieve this by comparing course component completion rates in arm 2 and arm 3 via a 1-way ANOVA in which the types of tips are used as the independent variable. We will then assess if age and gender predict which type of tip is the most engaging by using multiple regression.

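### The default home page may change on prompt use alone, and no stated analysis compares completion with arm 1, so a page with no benefit over control could be adopted

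*Protocol article*

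**What the plan says.** **Adoption.** Practical Implications (Discussion): "If we learn that the prompts are used by members, the arm 2 or arm 3 home page will become the default". The sentence covers new and existing members. It sets no level of use, asks for no comparison with arm 1, and does not say how arm 2 or arm 3 would be chosen.

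**Control arm.** Intervention Groups: "Members allocated to the first arm will be presented with a member home page that contains no behavioral prompts".

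**Aims.** The Objective includes "whether engaging with nudges and prompts increases engagement within the courses". The secondary outcome is to "test whether the presentation of tips and to-do items increases the overall completion of course content". Future Directions also describes the focus of the study as whether prompts raise engagement.

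**Analyses.** The primary outcome section begins "We will first measure engagement with the tips and to-do items in arms 2 and 3", and its tests are between those two arms: "All comparisons between arms 2 and 3 will be conducted by using an independent sample 1-tailed" *t* test. The secondary section compares completion in arms 2 and 3 by ANOVA on type of tip. The tertiary section uses the same two arms for engagement by type of tip.

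**Condition on the completion analysis.** Only the Abstract (Results) has it: "If members do engage, we will then, according to age and gender, examine whether nudges and prompts result in higher course completion rates".

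**The concern.** The adoption criterion and the research question do not match. Whether prompts increase completion can be answered only against members who had no prompts, which is what arm 1 provides. Prompt use does not exist in arm 1, so a criterion based on use cannot draw on the control arm. Clicks and completion are also different quantities. Members may click a tip and finish no more of the course than they would have done otherwise, or may read a tip, not click it, and go to the component anyway. Data Collection records tip shown, tip clicked and component completed separately, so the data allow this distinction.

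At stake is a platform-wide change made on evidence that does not address its benefit, while randomised control data that do address it go unused. If the Abstract's condition were followed literally, low click rates could also lead to the completion analysis being left out.

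**Working it through.** **1. Can the stated analyses show benefit over arm 1?** Set side by side:

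| Section | Quantity | Arms named |
|---|---|---|
| Primary outcome | engagement with tips and to-do items | 2 and 3 |
| Secondary outcome | course component completion | 2 and 3 |
| Tertiary outcome | engagement by type of tip | 2 and 3 |
| Power and Sample Size | at least 1 therapy session completed | 2 vs 3 (early figures labelled arms 1 and 2) |
| Practical Implications | prompts are used | 2 or 3 |

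No stated test includes arm 1. Even when completion is analysed, the result cannot show a gain over the control page.

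**2. How easily is the criterion met when completion does not change?** The article gives no threshold. Assume that use means at least one of n = 1414 members clicks, with member click rate c and independent members. Then P(met) = 1 − (1 − c)^1414.

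- c = 0.1%: 1 − 0.999^1414 = 1 − 0.243 = 0.757, about 76%
- c = 0.5%: 1 − 0.995^1414 = 1 − 0.0008 = 0.999, or 99.9%
- c = 1%: above 99.9%

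The effect on completion does not enter the formula. By contrast, a page with no effect would pass a two-sided .05 comparison with arm 1 in the favourable direction 2.5% of the time.

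**3. The article's own sample size.** Power and Sample Size prints 3.14% (arm 1, n = 510) and 5.79% (arm 2, n = 484) under the label power. I read them as proportions completing at least 1 session, since 16/510 = 3.14% and 28/484 = 5.79%. For 0.95 power at .05, the one-sided two-proportion formula gives 1313 per group, or 1387 with continuity correction, which is within 3% of the stated 1414. Two-sided, it gives 1576, or 1651 with correction. The stated figure is thus approximately reproduced as a one-sided calculation on these rates.

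**4. Power for a comparison with arm 1 at 1414 per arm, under that reading.** Power = Φ{[Δ√n − z·√(2p̄q̄)] / √(p₁q₁ + p₂q₂)}, with Δ = 0.0579 − 0.0314 = 0.0265, p̄ = 0.04465 and q̄ = 1 − p̄. Then Δ√n = 0.9965, √(2p̄q̄) = 0.2921 and √(p₁q₁ + p₂q₂) = 0.2915.

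- Two-sided .05 (z = 1.960): (0.9965 − 0.5725)/0.2915 = 1.455, power 92.7%
- Two-sided .025, the first Holm step for two comparisons (z = 2.241): (0.9965 − 0.6547)/0.2915 = 1.173, power 88.0%

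No arm 3 rate is given, so power for arm 3 vs arm 1 cannot be calculated.

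**5. Do the early figures already settle benefit?** SE = √(0.0314×0.9686/510 + 0.0579×0.9421/484) = 0.0131. The difference is 2.65 points, with 95% CI 2.65 ± 1.96×1.31, about 0.1 to 5.2 points. This is suggestive for arm 2, comes from an early look, and says nothing about arm 3.

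**The case against.** The adoption sentence is one line in the Discussion stating what the platform intends to do. It fixes no test or error rate, leaves the choice of page open, and does not say that other results will be ignored. It also fits Strengths and Limitations, which calls member engagement with prompts the primary purpose. All of this is fair, and it limits the weight of the point. It does not remove it. This is the only criterion the article gives for the default page, it covers all members, and the Objective, the secondary outcome and Future Directions state the comparative aim as well. Nor is the point about detail that an article leaves to a fuller document, because the criterion and the arms compared are both stated.

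Three stronger readings are tempting and are not supported.

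- *Adoption of an ineffective page is practically certain.* That depends on taking any click as use. Under a stricter meaning the probability cannot be computed from the article, and even under the lenient one it is 76% at a 0.1% click rate.
- *The completion analysis will be skipped if clicks are few.* The condition appears only in the Abstract. The secondary outcome section plans the completion analysis without it. This is an inconsistency to reconcile, not an established restriction.
- *The planned size supports the comparison at 93% power.* That figure is unadjusted, concerns arm 2 only, and relies on the reading of the printed percentages given above.

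It also stands that rewording the adoption sentence alone would achieve nothing, because the analysis it would depend on is not planned.

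**Conclusion.** The point holds in a limited form. As written, the plan permits a page with no completion benefit over control to become the default, and the control arm informs no stated decision. This follows from the text and needs no assumption. The 76% and 99.9% figures rest on the any-click definition of use and on independent members. The 93% and 88% figures rest on reading the printed percentages as arm 1 and arm 2 completion rates. A comparison with arm 1 at the planned size is feasible for arm 2, though below the article's 0.95 target. For arm 3 the power is unknown. The point merits correction but is moderate: the criterion is a statement of intent, and the randomised data needed for a better one have already been collected in all three arms.

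**What to change.** 1. In Secondary Outcomes, add comparisons of completion for arm 2 vs arm 1 and arm 3 vs arm 1 in all randomised members, two-sided at .05 with Holm adjustment for the two comparisons. Name the completion measure, since the section uses overall component completion and the power statement uses at least 1 therapy session.
2. Run these comparisons whatever the click rates, and remove the engagement condition from the Abstract so that it agrees with the Methods.
3. In Practical Implications, make the default-page change conditional on higher completion than in arm 1, and state how arm 2 or arm 3 is chosen if both qualify.
4. In the report, disclose that arm 1 and arm 2 were looked at early (November 1 to December 9, 2021) and that data collection had ended in May 2022, so that readers can judge when the comparison was specified.

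The cost is one added analysis of data already collected, some rewording, and a modest loss of power from adjustment (about 93% to 88% for arm 2 at the first Holm step, under the assumed rates).

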### Strengths and Limitations

A strength of this experiment is that it will be conducted in an ad libitum environment. Unlike most digital health studies, ours will not be conducted with a small population in a controlled environment. Further, members will not be aware of the experiment, which will limit participant bias and the Hawthorne effect.

A limitation of this experiment is that, especially due to the anonymity of members, we have no way of knowing who members are. We have no way of knowing whether registrants are people with depression or anxiety who are seeking help, or are browsing for other reasons. However, we have exceeded sample size requirements and believe that the large number of subjects should dampen these effects on the results.

A final limitation is that not all white-label clients license all course components. For example, some community tools and the depression and anxiety test are feature flags that are not used by all white-label clients. As the primary purpose of this experiment is to test whether members engage with prompts and nudges, we do not expect this particular limitation to hamper the overall results.

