#### Behavioral Prompts

In applied behavioral analysis, behavioral prompts are cues that are specifically designed to encourage individuals to perform a specific task [34]. In our study, we will be employing the following two types of behavioral prompts, which are anchored in nudge theory: daily tips and a to-do checklist (Table 1).

Figure 1 is an example of a present bias tip that could randomly appear on a member’s main home page.

**Table 1 table1:** Example nudges and prompts.

Delivery format	Content type	Text example from our study
Tip	Directive content	“Express yourself by uploading your own image!”
Tip	Social proof	“Many members have similar goals as yours. Reviewing other members' goals can help you reach your own.”
Tip	Present bias	“Feel better sooner by learning from others. Read what others have posted on the community.”
Prompt	To-do checklist	“Watch the Getting Started Video”

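### Completion and to-do counts ignore which components a member's client has licensed, so the age and gender comparisons may be confounded by licensing

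*Protocol article*

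**What the plan says.** Strengths and Limitations in the protocol article says that clients do not all license every course component, and gives as examples that "some community tools and the depression and anxiety test are feature flags that are not used by all white-label clients". It sets this aside with one reason, the trial's main purpose: "As the primary purpose of this experiment is to test whether members engage with prompts and nudges, we do not expect this particular limitation to" matter for the results overall.

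The measures are fixed under Primary Outcome:
- Tips: "the number of tips that a member clicked divided by the number of tips that were presented to the member".
- To-do list: "Engagement with to-do items will be measured as the number of to-do items that a member clicked".
- Completion: "course component completion rates will be measured as the number of course components that a member completed". It is called a rate but has no denominator.

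The primary outcome is to be compared by age and gender. The Abstract (Results) says completion will also be examined by age and gender. The secondary analysis is described as "comparing course component completion rates in arm 2 and arm 3 via a 1-way ANOVA". The tertiary analysis is an ANOVA of tip engagement by tip type. Each is followed by a regression in which age and gender are the only predictors named. No term for client or feature availability appears in any of these.

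**The concern.** A member cannot complete a component that the client has not licensed. On a raw count, that member looks the same as one who had the component and ignored it. The appeal to the primary purpose does not answer this. The stated objective has a second part, whether prompts raise engagement within the courses, and that part is measured by the completion count. The to-do count sits under the primary outcome itself.

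Age and gender are not randomised. The Digital Health Platform section lists employers, insurers and educational institutions among the clients. If their memberships differ in age or gender and their licences differ too, a licensing gap would be read as a difference in interest. Future Directions intends to customise content for gender and demographic groups on these findings and then to study its effectiveness.

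**Working it through.** The article gives no figure for how many clients or members lack a feature, so there is no stated number to reproduce. What follows is a count from Table 4 and then illustrations under labelled assumptions.

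**1. How many components could be affected.** Table 4 tracks 14 actions. Community-type actions are 4, 5, 6, 9, 12, 13 and 14 (7 actions), and the test is action 10, so 7 + 1 = 8 of 14. The to-do list is actions 1, 2, 3, 4, 7, 8, 10 and 11 (8 items), of which 4 and 10 are in the affected set, so 2 of 8. Both are upper bounds for the features named, because the article says only some community tools are flagged. Cognitive behavioral therapy sessions are not among the features named, so the endpoint used for the sample size is not touched on what is stated.

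**2. What the count does.** Completion of an unlicensed component is necessarily zero. A to-do item is also necessarily zero if it is hidden. If it is displayed it might still be clicked, and the article does not say which happens.

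**3. Between arms.** Members are individually randomised, so the share lacking a feature, u, has the same expectation in each arm. With an assumed u = 0.30 and the planned 1414 per group, the SD of the chance difference is √(2 × 0.30 × 0.70 / 1414) = 0.017, about 1.7 percentage points. Missing features lower both arms alike and create no arm difference where there is no effect.

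**4. Between age or gender groups.** Assume a true completion rate of 10% for every available component, k components flagged, and a share u of the group without them. The expected count is 0.10 × (14 − k·u).

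| Lacking access, group A / B | k | Count A | Count B | B relative to A |
|---|---|---|---|---|
| 20% / 20% | 1 or 8 | equal | equal | 0 |
| 10% / 30% | 1 | 1.39 | 1.37 | −1.4% |
| 10% / 30% | 8 | 1.32 | 1.16 | −12.1% |
| 10% / 50% | 1 | 1.39 | 1.35 | −2.9% |
| 10% / 50% | 8 | 1.32 | 1.00 | −24.2% |

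The relative gap does not depend on the 10%. For the third row it is (14 − 8 × 0.3)/(14 − 8 × 0.1) = 11.6/13.2 = 0.879 for any common rate. The gap is zero if access is equal across groups.

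**5. Tip clicks by type.** Suppose tips for unlicensed components are still shown and never clicked, every tip has a true click rate of 10%, and a fraction c of a type's tips point to flagged components. The observed rate is 0.10 × (1 − u·c). With u = 0.30, c = 0.3 for directive tips and c = 0.7 for arm 3 tips, this gives 9.1% and 7.9%, a false difference of −1.2 points. Over u = 10% to 50% its size is 0.4 to 2.0 points. With c reversed the sign reverses. The difference is zero if c is equal, if such tips are suppressed, or if they can be clicked as readily as any other.

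**6. Scoring over what is enabled.** Under the assumptions of step 4, a member with all 14 components has 1.4/14 = 10%, and one with 6 enabled has 0.6/6 = 10%, so the artefact disappears. If components differ in how often they are completed, the proportion still depends on which ones are enabled, which is why a model term is needed as well.

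**The case against.** The authors disclose the limitation, and much of the case against making more of it stands.

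- **Tip clicks.** A reader might infer that members without a feature are counted as not engaging with tips. The article does not say so. The denominator is tips presented, completion is tracked as a separate behaviour, and the display rule for unlicensed tips is not given.
- **Tip type.** A reader might infer from Table 1 that arm 3's tips lean on the community and are therefore penalised. Table 1 shows one example per type, out of 35 + 15 + 15 = 65 tips, and Table 4 does not split components by tip type. The social proof example, "Reviewing other members' goals can help you reach your own", concerns goals, and Table 3 lists the goals exercise apart from the moderated community, so it may not be a flagged tool at all.
- **Arms.** Randomisation protects the arm 2 versus arm 3 completion comparison in expectation. The checklist exists only in arm 3, so its two possibly unlicensed items cannot distort an arm contrast of to-do clicks.
- **Age and gender.** No section says that client mix or licensing varies with age or gender.

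It can also be said that covariates and display rules belong in an analysis plan that is not shown. That is fair for what is left unsaid. It does not answer what is said: the article fixes two outcomes as raw counts, and it draws a conclusion about validity from a reason that does not extend to completion or to age and gender.

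**Conclusion.** The point holds in a limited form. The completion count, and the to-do count where items are hidden, mix willingness with access. Up to 8 of 14 components and 2 of 8 to-do items could be involved. The comparisons by age and gender may be confounded by licensing. Under assumed access gaps of 20 to 40 percentage points between groups, the false difference in the completion count runs from 1.4% to 24%, and it is zero if access does not vary with age or gender. Neither its size nor its direction can be established from the article.

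The comparison between arms is not biased in expectation. A bias between tip types would need unlicensed tips to be shown, to go unclicked for that reason, and to make up different shares of the tip types. None of these is stated, so that bias is a possibility to rule out and not a finding.

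**What to change.** - **Primary Outcome and Secondary Outcomes:** score completion as components completed over components enabled for the member's client, and to-do engagement as items clicked over items enabled.
- **Tip engagement:** state whether tips and to-do items for unlicensed components are displayed. If such tips are displayed, count only tips for enabled components, in both numerator and denominator.
- **Models:** add client licence type or feature availability as a factor in the age/gender and tip-type analyses under Primary, Secondary and Tertiary Outcomes.
- **Strengths and Limitations:** limit the reassurance to the between-arm comparison, and say that the counts and the age/gender comparisons depend on licensing.

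Data collection ended in May 2022, but all of this can be done at analysis. It needs the feature-flag settings merged with the member records, assuming the platform still holds the settings that applied during the trial. The price is that merge, smaller denominators for some members, and one added model factor.
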